# Comparison of different intervention methods to reduce the incidence of venous thromboembolism: study protocol for a cluster-randomized, crossover trial

**DOI:** 10.1186/s13063-023-07868-y

**Published:** 2023-12-19

**Keywords:** Venous thromboembolism, Orthopedic trauma patients, Low molecular weight heparin, Cluster-randomized crossover

## Abstract

**Background:**

Venous thromboembolism (VTE) remains a priority challenge among orthopedic trauma patients. It is crucial to further improve the prophylaxis against VTE in routine orthopedic treatment. This study aims to compare the efficacy of two low molecular weight heparin (LMWH) regimens and additional intermittent pneumatic compression in preventing VTE among orthopedic trauma patients.

**Methods and analysis:**

This is a cluster-randomized crossover clinical study conducted in four hospitals in Shanghai from December 2019 to December 2023. The unit of randomization is orthopedic wards, and each ward will define a cluster. All clusters will implement four diverse intervention measures and one control measure in a given random sequence. Perioperative orthopedic trauma patients aged ≥ 18 years with stable vital signs, Caprini score > 2, and no contraindication of anticoagulation or intermittent pneumatic compression (IPC) devices will be eligible. The sample size will be determined to be 2590, considering cluster effect, period effect, and interactions. We will generally use the intention-to-treat (ITT) at the subject level for each outcome. For the primary outcome of the study, the incidence of VTE will be presented as risk ratio and 95% CIs. Generalized estimating equation (GEE) will be deployed to compare differences and adjust cluster effect, period effect, and interaction among interventions and periods if applicable.

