## Background

Venous thromboembolism (VTE) refers to the abnormal coagulation of blood in the vein, causing complete or incomplete occlusion of blood vessels, which belongs to venous reflux disorder disease [1]. It has been documented that 40–60% of surgical or medical patients remained at risk of VTE, ranking as the third most common cardiovascular disease following heart attack and cerebral infarction [2, 3]. However, VTE prophylaxis remains underused. The ENDORSE study found that only 40% of at-risk medical patients received VTE prophylaxis in 32 countries [4]. Recently, our retrospective cohort study confirmed that approximately 60% of orthopedic trauma patients received VTE prophylaxis, which was considerably higher compared to previous studies. However, VTE incidence was determined to be 19% [5], similar to that among the orthopedic trauma patients without receiving prophylaxis in Canada [6]. This finding raised a concern in the effectiveness of VTE prophylaxis.

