### Proposed sample size

We determined the sample size based on the cumulative incidence of VTE. It is estimated that at least 398 orthopedic trauma patients need to be enrolled in each of the five clusters to achieve a power value of 85% to detect an absolute difference of 10% in the cumulative incidence of VTE between the patients with intervention measures and those with control measures (assuming a VTE incidence of 15% according to our retrospective cohort study [5]) at a two-sided alpha level of 0.05. Consequently, approximately 40 patients will be enrolled per intervention measure/control measure per calendar month in each cluster, totaling 1990 patients. The intraclass correlation coefficient (ICC) was calculated based on two levels, 0.228 for patients within the same cluster/time period and 0.15 for patients within the same cluster/different time periods. Due to the lack of data on ICCs related to the current study design and primary outcome, we chose to use a conservative ICC value in our sample size estimation. Moreover, considering a 20% loss of participants, we determine to enroll a total of 2490 patients in the trial, with 498 in each cluster.

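### The abstract's sample size of 2590 conflicts with the 2490 that the plan's own inputs give, and the planning VTE incidence of 15% is credited to a cohort that the Background reports at 19%

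*Protocol article*

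**What the plan says.** Two planning figures each appear with two values in the Protocol article.

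- **Total sample size.** The abstract (Methods and analysis) has "The sample size will be determined to be 2590, considering cluster effect, period effect, and interactions". The section Proposed sample size starts from "at least 398 orthopedic trauma patients need to be enrolled in each of the five clusters", gives a total of 1990 before loss, and then, "considering a 20% loss of participants", arrives at "we determine to enroll a total of 2490 patients in the trial, with 498 in each cluster".
- **VTE incidence.** Proposed sample size sets the calculation "to achieve a power value of 85" percent for a 10-point absolute difference between intervention and control at two-sided 0.05, "assuming a VTE incidence of 15% according to our retrospective cohort study [5"]. The Background, describing the authors' own retrospective cohort, says "VTE incidence was determined to be 19% [5"]. It adds that about 60% of those patients received prophylaxis.

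Under Interventions, the control measure has no prescribed regimen; prophylaxis is left to the treating orthopedists.

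**The concern.** The recruitment target and the assumed event risk both underlie the trial's claim to adequate power, and each should have one value.

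The two totals differ by 100 patients, and the abstract is where most readers will look for the target.

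The incidence conflict matters more. Both figures are credited to the same cohort under the same reference number, and the text gives no subset, period or outcome definition that would account for the gap. The cohort as described (routine care, part of the patients on prophylaxis) is close to what the control wards will deliver. If control patients have VTE at 19% and not 15%, the binomial variance is larger, and the same 10-point difference needs more patients or is tested with less power.

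**Working it through.** **1. Total sample size**

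Inputs, all from Proposed sample size: 398 per ward, five wards, 20% loss.

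- Before loss: 5 × 398 = 1990, as stated.
- Per ward after loss: 398 / (1 − 0.20) = 497.5, rounded up to 498, as stated.
- Total: 5 × 498 = 2490, as stated. Inflating the total directly gives 1990 / 0.80 = 2487.5, the same apart from rounding.

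The abstract's figure does not follow:

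- 2590 / 5 = 518 per ward, a number that appears nowhere.
- 1 − 1990/2590 = 23.2% loss, against the stated 20%.
- Multiplying by 1.2 instead of dividing by 0.8 gives 1990 × 1.2 = 2388, which is not 2590 either.

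**2. Incidence: number per measure before clustering**

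Inputs: two-sided alpha 0.05 (z = 1.960), power 85% (z = 1.036), absolute difference 0.10 (Proposed sample size); control risk 15% (Proposed sample size) or 19% (Background). The difference is taken as a reduction, in line with the stated hypothesis.

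Formula (unpooled): n = (1.960 + 1.036)² × [p1(1 − p1) + p2(1 − p2)] / (p1 − p2)², with (1.960 + 1.036)² ≈ 8.978.

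| Control v intervention | Variance sum | n per measure |
|---|---|---|
| 15% v 5% | 0.1275 + 0.0475 = 0.1750 | 8.978 × 0.1750 / 0.01 ≈ 157 |
| 19% v 9% | 0.1539 + 0.0819 = 0.2358 | 8.978 × 0.2358 / 0.01 ≈ 212 |

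The ratio is 0.2358 / 0.1750 = 1.35, or 35% more. The pooled-variance version gives 161 and 215, or 34% more.

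Reading 15% as the intervention risk does not remove the conflict: a 10-point reduction would then imply a control risk of 25%, which does not match 19% either.

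**3. Incidence: effect on power after clustering**

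The article states two ICCs (0.228 within a ward-period, 0.15 between periods of the same ward) but no design-effect formula. I assume the usual cluster-crossover form, 1 + (m − 1) × 0.228 − m × 0.15, equal allocation (1990 / 5 = 398 per measure), and about 40 patients per ward-month (m = 39.8).

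- Design effect: 1 + 38.8 × 0.228 − 39.8 × 0.15 = 1 + 8.846 − 5.970 = 3.88.
- Effective number per measure: 398 / 3.876 ≈ 102.7.
- 15% v 5%: SE = √(0.1750 / 102.7) = 0.0413; 0.10 / 0.0413 − 1.960 ≈ 0.46; power ≈ 68%.
- 19% v 9%: SE = √(0.2358 / 102.7) = 0.0479; 0.10 / 0.0479 − 1.960 ≈ 0.13; power ≈ 55%.

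The pooled-variance version gives about 67% and 54%.

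**The case against.** - **The 2590 is only a slip.** The sample size section fixes the total both overall and per ward, so a reader might say that nothing is in doubt. It probably is a typing error, and I would not infer that a larger trial was planned. But the abstract is current text, it states the target, and it is wrong as written.
- **15% may be legitimate.** The cohort report is not at hand, and neither place labels its figure a control risk. The trial excludes patients with VTE at enrollment and those with hepatic or renal dysfunction, and its outcome appears to concern VTE found after surgery. A comparable subset of the cohort could show 15%, although the Caprini score criterion could push the other way. This stands. A reader might infer that 19% is the right control risk; the documents show only that the two figures are unreconciled.
- **The power loss depends on the absolute difference.** Also true. Keeping the relative reduction instead (19% v 6.3%), the number per measure falls to about 119 and power under the same assumptions is about 79%. But the plan specifies its effect as an absolute 10 points.
- **The design effect is assumed.** It is, and the normal approximation with five wards is rough. The 68% at the plan's own 15% is below the claimed 85%, but that gap is a separate question from the incidence conflict. Only the step from 68% to 55% belongs here.

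Two further inferences are tempting and not supported:

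- A reader might say that 498 per ward contradicts 40 per month. The article says "approximately 40 patients will be enrolled per intervention measure/control measure per calendar month in each cluster, totaling 1990 patients", which ties that rate to the total before loss. The ten periods of Fig. 1 are labelled hypothetical, and at 40 per month 498 patients take about 12.5 months (498 / 40).
- A reader might say that the abstract's mention of interactions is false because the calculation shows no such term. A condensed article's silence does not establish that.

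**Conclusion.** Both conflicts hold.

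The sample size conflict is certain: 2490 is the only total that the stated inputs give, and the abstract overstates it by 100 patients, about 4%. It is easily corrected and does not by itself affect the design.

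The incidence conflict carries the weight. The same cohort and reference are credited with 15% and 19%, with no explanation, and the 19% comes from a setting that resembles the control. Which figure suits this trial's population cannot be settled from the article. If it is 19% and the 10-point difference stands, 35% more patients per measure are needed before clustering; this depends only on the two-proportion formula. The fall in power from about 68% to about 55% rests in addition on the assumed design effect, equal allocation at 398 per measure, about 40 patients per ward-month and a normal approximation. It should be read as an indication of size.

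**What to change.** 1. Change 2590 to 2490 in the abstract.
2. Reconcile 15% with 19% in Proposed sample size. Either state which subset or outcome definition in the cohort yields 15% and why it matches the trial's eligible patients and endpoint, or plan on 19% and restate the power for the 10-point difference.
3. In either case, say explicitly that the figure is the control risk, if that is what is meant, and give the design-effect formula used with the two ICCs so that the stated power can be checked.

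The first change is a one-number correction. The second costs a sentence if a 15% subset exists; otherwise it costs a recalculation and probably a less favourable stated power. With recruitment expected to end in December 2023, the practical use is an accurate record of what the trial could detect, so that a null result is read correctly.

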**Discussion:**

VTE is a complication that cannot be underestimated after major orthopedic surgery. Early identification, early assessment, and early prevention can significantly reduce the incidence of VTE. Most guidelines recommend both medical and physical prevention, and we hope to demonstrate how they would affect the incidence among perioperative orthopedic patients. We want to explore if there is a difference between the two types of LWMH with or without an IPC device to provide more evidence for future guidelines and prevent more patients from the threat of VTE.

**Ethics and dissemination:**

The study received approval from the IRB of the coordinating center and all participating hospitals. Findings will be disseminated through peer-reviewed publications and conference presentations.

**Trial registration:**

ChiCTR1900027659. Registered on 17 November 2019

**Supplementary Information:**

The online version contains supplementary material available at 10.1186/s13063-023-07868-y.

## Background

Venous thromboembolism (VTE) refers to the abnormal coagulation of blood in the vein, causing complete or incomplete occlusion of blood vessels, which belongs to venous reflux disorder disease [1]. It has been documented that 40–60% of surgical or medical patients remained at risk of VTE, ranking as the third most common cardiovascular disease following heart attack and cerebral infarction [2, 3]. However, VTE prophylaxis remains underused. The ENDORSE study found that only 40% of at-risk medical patients received VTE prophylaxis in 32 countries [4]. Recently, our retrospective cohort study confirmed that approximately 60% of orthopedic trauma patients received VTE prophylaxis, which was considerably higher compared to previous studies. However, VTE incidence was determined to be 19% [5], similar to that among the orthopedic trauma patients without receiving prophylaxis in Canada [6]. This finding raised a concern in the effectiveness of VTE prophylaxis.

It is routinely recommended initiating low molecular weight heparin enoxaparin (LMWH) as pharmacological prophylaxis for orthopedic trauma patients [7]. Multiple studies focused on monitoring plasma anti-Xa levels to adjust the dosage of LMWH administered to orthopedic trauma patients [7]. It suggested that the best dosage would be achieved when administering at least the third dose of LMWH [8]. Compared with a fixed dosage, a weight-based dosage may be more effective in reaching the expected anti-Xa level [9]. Additionally, weight has been proven to be a key predictor of anti-Xa levels [10]. Thus, our study is designed to administer a weight-based dosage of LMWH, instead of a fixed dosage as usual, to achieve a better effect in preventing VTE. Our retrospective cohort study found that varying dosage as well as diverse LMWH regimens had different prophylaxis effects, as described elsewhere [11]. Moreover, intermittent pneumatic compression (IPC) is used as mechanical prophylaxis when patients have a contraindication to pharmacological prophylaxis [12, 13]. However, previous studies have been limited by non-randomized design, small sample size, and negative findings, when recommending IPC for orthopedic trauma patients [14, 15]. Furthermore, whether the combination of IPC and LMWH may reduce the risk of VTE remains uncertain [16]. Therefore, we decided to design and perform a cluster-randomized crossover trial to further determine the efficacy of multiple interventions in preventing VTE among orthopedic trauma patients.

### Hypothesis and outcomes

The hypothesis is that the combination of LMWH and IPC can reduce the risk of VTE. The primary outcome of this study is the incidence of VTE, defined as on VTE observed before the orthopedic surgery, while any form of VTE identified after the surgery. The secondary outcomes included the amount of bleeding during operation and mortality within 30 days.

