### Data analysis

#### Statistical analysis principles

We will generally perform the analysis using the intention-to-treat (ITT) at the subject level for each outcome. All the participants with a recorded outcome will be included in the analysis according to the intervention group to which they have been randomized. Additionally, we will take the cluster-randomized crossover design effect into consideration. Adjustment for multiple comparisons among interventions will be used. The SAS 9.4 software will be used for all statistical analyses.

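### The stated power covers intervention v control at 0.05 only: none is given for the IPC add-on contrast, nor at the alpha left after the planned multiplicity adjustment

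*Protocol article*

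**What the plan says.** Under Hypothesis and outcomes, the protocol article gives one hypothesis: "The hypothesis is that the combination of LMWH and IPC can reduce the risk of VTE". It does not say compared with what.

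Other sections suggest the comparator. The Background says that "whether the combination of IPC and LMWH may reduce the risk of VTE remains uncertain". The abstract's Background gives the aim as comparing two LMWH regimens and additional IPC, and the abstract's Discussion says "We want to explore if there is a difference between the two types of LWMH with or without an IPC device". Under Interventions, measures 3 and 4 are measures 1 and 2 with IPC added. The control is prophylaxis at the orthopedist's discretion.

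Proposed sample size aims for 85% power against a 10-point absolute difference. The contrast it sizes is "between the patients with intervention measures and those with control measures", and the test is made "at a two-sided alpha level of 0.05". It cites an incidence of 15%, ICCs of 0.228 (same ward, same period) and 0.15 (same ward, different periods), about 40 patients per ward-month, 398 per cluster and 1990 in total. It mentions no adjusted alpha.

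Statistical analysis principles then says: "Adjustment for multiple comparisons among interventions will be used". It names neither the method nor the set of comparisons.

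**The concern.** Three statements do not line up. The hypothesis is about the combination, most naturally IPC on top of LMWH. The sample size concerns any intervention against usual care. The alpha in the sample size is the full 0.05, whereas the analysis is to be adjusted.

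A reader who sees 85% power may take it to cover the stated hypothesis under the planned tests. It covers neither the add-on contrast nor, as written, an adjusted test. If IPC adds a modest benefit to LMWH, a non-significant result could be read as evidence that IPC does not help, when the comparison was never sized. It also matters which patients enter the contrast. Comparing each LMWH with and without IPC separately uses about 398 v 398. Pooling over both LMWHs uses about 796 v 796 from the same trial.

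**Working it through.** **Inputs.** From Proposed sample size: two-sided alpha 0.05, power 85%, 10-point difference, 15% incidence, ICCs 0.228 and 0.15, about 40 per ward-month, 1990 patients. With five measures, 1990/5 = 398 per measure, the same number as per cluster.

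**1. The plan's own figure.** The standard two-proportion formula at 0.05 and 85% power, without clustering, gives 161 per arm for 15% v 5% and 286 for 25% v 15% (the text does not say which arm has 15%). The cluster-crossover design effect is

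DE = 1 + (40 − 1) × 0.228 − 40 × 0.15 = 1 + 8.892 − 6 = 3.892.

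Applying it to the unrounded values: 160.05 × 3.892 ≈ 623 and 285.75 × 3.892 ≈ 1112 per arm. None of these is 398. Two unstated routes reach it:
- 25% v 15% at 0.05/4 = 0.0125 with no clustering: 397.8.
- 25% v 15% at 0.05 with 8 patients per ward-period (DE 1.396): 398.9.

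The loss step does reproduce: 1990/0.8 = 2488, about 2490.

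**2. Power formula for the checks below.**

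SE = √[(p1q1 + p2q2) × DE/n], power = Φ(|p1 − p2|/SE − z).

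Here z = 1.960 at 0.05 and 2.498 at 0.0125. For one pair n = 398, so DE/n = 3.892/398 = 0.00978. For the contrast pooled over both LMWHs n = 796. The ward effect cancels, so the SE falls by √2.

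**3. The sized contrast: one measure v control, 15% v 5%.**
- p1q1 + p2q2 = 0.1275 + 0.0475 = 0.175.
- SE = √(0.175 × 0.00978) = 0.0414, and 0.10/0.0414 = 2.417.
- At 0.05: Φ(0.457) = 68%.
- At 0.0125 (assumed Bonferroni over four measures v control): Φ(−0.080) = 47%.
- Without clustering (DE = 1) the same comparison has 99.7% at 0.05 and 99% at 0.0125.

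The ICCs therefore cause most of the loss. Multiplicity adds to it: holding 85% at 0.0125 takes ((2.498 + 1.036)/(1.960 + 1.036))² = 1.39 times the patients.

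**4. The IPC add-on contrast, LMWH alone v LMWH + IPC.** The documents give no IPC effect, so all the rates here are assumptions. For 10% v 5%: p1q1 + p2q2 = 0.09 + 0.0475 = 0.1375. The pair SE is 0.0367 (ratio 1.364) and the pooled SE is 0.0259 (ratio 1.928). Power at 0.05:

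| Assumed rates | One pair, DE 3.892 | Pooled, DE 3.892 | One pair, DE 1 | Pooled, DE 1 |
|---|---|---|---|---|
| 10% v 5% | 28% | 49% | 77% | 97% |
| 5% v 2.5% | 15% | 27% | 46% | 75% |
| 15% v 10% | 19% | 33% | 57% | 86% |
| 15% v 7.5% | 40% | 68% | 92% | 99.7% |

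At 0.0125 with DE 3.892, 10% v 5% has 13% for one pair and 28% pooled.

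These are normal approximations. With only five wards, true power is probably lower.

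**The case against.** The strongest reply is that the hypothesis names no comparator. Read as combination v usual care, it is one of the contrasts that was sized. The article also describes the trial as exploratory and its aim as the efficacy of multiple interventions. This stands as far as it goes: the add-on reading is likely but inferred. The trial nevertheless states a hypothesis, a power and an alpha, so they should refer to the same test.

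The adjustment method and the list of contrasts are properly left to an analysis plan. That is accepted, and their absence here is not the point. The 0.0125 level is an assumption of this check. A reader might infer that the alpha will be split over many pairwise tests, or that the analysis ignores the 2×2 arrangement of LMWH type and IPC. The documents say neither, and the planned GEE can accommodate a pooled contrast.

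The 398 may already contain an unreported Bonferroni split, since 25% v 15% at 0.0125 without clustering gives it. That would contradict the stated 0.05 and leave the stated ICCs unused. An unadjusted route fits about as well, so the text cannot settle it.

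A reader might also infer that a 10-point effect is impossible for IPC, because LMWH alone would leave only 5% to act on. That requires 15% to be the control rate and LMWH alone to achieve the whole reduction. The documents state neither.

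Finally, most of the low power reflects the ICCs rather than the choice of contrast or the multiplicity. This is correct.

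**Conclusion.** The point holds in limited form. The stated 85% refers to intervention v control at 0.05. As written, it does not apply to the adjusted tests, and no power is stated for IPC added to LMWH. On the plan's own ICCs and ward-month size, even the sized contrast (read as 15% v 5%) reaches about 68% at 0.05, and about 47% at an assumed 0.0125. For an assumed IPC effect of 10% v 5%, power at 0.05 is about 28% per LMWH pair and 49% pooled.

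The stronger conclusion, that the trial cannot answer its own hypothesis, is not supported. The documents give no IPC effect, and pooled power at 0.05 in the scenarios above runs from 27% to 99.7%, depending on that effect and on how much clustering there is. The conclusion rests on the add-on reading of the hypothesis, 398 analysed per measure and the stated ICCs.

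**What to change.** Before outcome data are analysed:

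- Name the comparator in the hypothesis. State the IPC contrast as IPC v no IPC (measures 3+4 v 1+2), adjusted for LMWH type in the GEE, with the LMWH-by-IPC interaction reported as a check.
- State which comparisons fall under the multiplicity adjustment and the alpha for each.
- Restate power for the IPC contrast and for each measure v control, at that alpha and with the stated ICCs.

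The cost is wording and a recalculation, with the same patients. There are two downsides. The pooled contrast assumes that IPC acts similarly with both LMWHs. The restated power will also fall below 85% in plausible scenarios. Pooling improves precision but does not by itself make the power adequate, and the report should say so.
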